## Abstract

**Background:**

In patients with clinically suspected appendicitis, imaging is needed to substantiate the clinical diagnosis. Imaging accuracy of ultrasonography (US) is suboptimal, while the most accurate technique (CT) is associated with cancer related deaths through exposure to ionizing radiation. MRI is a potential replacement, without associated ionizing radiation and no need for contrast medium administration. If MRI is proven to be sufficiently accurate, it could be introduced in the diagnostic pathway of patients with suspected appendicitis, increasing diagnostic accuracy and improving clinical outcomes, without the risk of radiation induced cancer or iodinated contrast medium-related drawbacks. The multicenter OPTIMAP study was designed to estimate the diagnostic accuracy of MRI in patients with suspected acute appendicitis in the general population.

**Methods/Design:**

Eligible for this study are consecutive patients presenting with clinically suspected appendicitis at the emergency department in six centers. All patients will undergo imaging according to the Dutch guideline for acute appendicitis: initial ultrasonography in all and subsequent CT whenever US does not confirm acute appendicitis. Then MRI is performed in all patients, but the results are not used for patient management. A final diagnosis assigned by an expert panel, based on all available information including 3-months follow-up, except MRI findings, is used as the reference standard in estimating accuracy. We will calculate the sensitivity, specificity, predictive values and inter-observer agreement of MRI, and aim to include 230 patients. Patient acceptance and total imaging costs will also be evaluated.

**Discussion:**

If MRI is found to be sufficiently accurate, it could replace CT in some or all patients. This will limit or obviate the ionizing radiation exposure associated risk of cancer induction and contrast medium induced nephropathy with CT, preventing the burden and the direct and indirect costs associated with treatment. Based on the high intrinsic contrast resolution of MRI, one might envision higher accuracy rates for MRI than for CT. If so, MRI could further decrease the number of unnecessary appendectomies and the number of missed appendicitis cases.

**Trial registration:**

NTR2148

## Background

Acute appendicitis is one of the most common reasons for acute abdomen [1]. Diagnosis based on clinical evaluation only is difficult and results in high negative appendectomy rates and missed diagnoses [2,3]. Negative appendectomies increase mortality, prolong hospital stay, and increase the risk of infectious complications [4]. Appendicitis is missed in approximately 12% of patients, increasing the risk of perforated appendicitis, peritonitis, abscesses and leading to a two to tenfold increased mortality rate [5-7].

The use of ultrasonography (US) and computed tomography (CT) to support clinical diagnosis is widespread [8]. US has considerable accuracy limitations, as it generates too many false negative results. Although CT is more accurate, it fails in 12% of patients and results in considerable ionizing radiation exposure in often young individuals. This ionizing radiation exposure is associated with the risk of cancer induction and cancer related death [9]. Iodinated contrast medium administration may also induce nephropathy or aggravate existing nephropathy.

MRI is a potential replacement for CT, without associated ionizing radiation and contrast medium administration. If proven to be sufficiently accurate, MRI could be introduced in the diagnostic pathway of patients with suspected appendicitis, increasing diagnostic accuracy and improving clinical outcome, without the risk of radiation induced cancer or iodinated contrast medium-related drawbacks.

Available studies on the diagnostic accuracy of MRI are limited in size, single center and primarily included selected patients - often pregnant women - with a different spectrum and prevalence of disease compared to the general population. In these studies 10% of patients had appendicitis, substantially lower than the usual 60%. Experience with newer MRI techniques that may boost its accuracy, such as diffusion-weighted imaging (DWI), is even more limited.

These results do not justify introducing MRI as first line imaging technique in patients suspected for acute appendicitis yet. To evaluate the potential of MRI as an alternative imaging method in patients with suspected appendicitis, we need a sufficiently powered study in unselected patients. The present study will allow us to estimate the accuracy of MRI in unselected patients and to compare with that of CT. This may help us to identify the optimal diagnostic strategy, selecting from available imaging modalities, aiming at high diagnostic accuracy without compromising health care while minimizing radiation exposure.

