### Study design

OPTIMAP is a multicenter diagnostic accuracy study of MRI in a consecutive series of adult patients with clinically suspected acute appendicitis. Consenting patients will undergo initial ultrasonography followed by CT in all cases in which US does not confirm the suspected appendicitis, which is the strategy specified in the Dutch guideline for suspected acute appendicitis. Additionally, all patients undergo MRI, with the MRI reader blinded from the results of the other imaging methods. A final diagnosis assigned by an expert panel based on all available data (except MRI) after 3 months follow-up will act as the reference standard in estimating accuracy.

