### Data Analysis

Data analysis primarily will focus on the diagnostic accuracy of MRI in correctly identifying patients with appendicitis. Sensitivity, specificity, positive and negative predictive value of MRI in detecting acute appendicitis will be calculated with corresponding 95% confidence intervals, by comparing the results of MRI, as read by trained radiologists and the MRI expert panel, with the final diagnosis assigned by the expert panel. In addition, the accuracy of the following scenarios will be estimated: (1) Clinical evaluation without imaging, (2) US in all patients followed by CT after a non diagnostic US, (2) US only, (3) MRI only, (4) US followed by MRI after a non diagnostic US. A gain in diagnostic value of strategies using two tests will be evaluated using the likelihood ratio based method proposed by McAskill and colleagues [10]. Next, we will evaluate the diagnostic performance of stratified imaging strategies taking into account patient characteristics (e.g. age, gender) and presentation features (e.g. duration of complaints). We will also investigate accuracy modifiers, such as body mass index and gender, which are known to influence the diagnostic performance of some imaging modalities.

For the cost evaluation, we will estimate and compare the total imaging costs for each imaging strategy. Standard unit prices will be used for all imaging modalities. Total imaging costs in multi-modality strategies will be driven by the positivity rate of the first imaging procedure.

To evaluate inter-observer agreement we will calculate percentage agreement and kappa values for the diagnosis of appendicitis in MRI between observer 1 en 2 (clinical practice reading) en central reading. Effects of reader experience will be evaluated by comparing the accuracy of local reading (single observer) to the accuracy of the expert central reading.

We will evaluate patient acceptance of MRI in comparison to standard imaging practice as documented in the Dutch guidelines. For each examination participants are invited to rate their experience (including burden, discomfort and pain) using five-point Likert scales (none, mild, moderate, severe, extreme). Differences between US, CT and MRI will be tested for statistical significance.

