## Discussion

Abdominal MRI has often been associated with lengthy examination times, which would make it less appropriate for evaluating acute appendicitis. Yet examination time should no longer be a hurdle: with present-day hardware and software, imaging protocols with 15 minutes in-room time suffice for evaluating a patient with suspected appendicitis. MRI is already used for other acute primarily neurological conditions, such as imminent paraplegia. With limited requirements for room time, the availability of MRI for evaluating acute conditions can be expanded to include acute appendicitis, as is already possible in the institutions participating in this study. Our study group is performing a national survey, to evaluate MRI availability for acute diagnosis and identify potential hurdles for the introduction of acute MRI at a national level.

The American College of Radiology has published a consensus document on appropriateness criteria for imaging evaluation of patients with acute pain in the right lower quadrant. The consensus finds CT the most appropriate for these patients [17]. Recently we have published the results of a preceding study in patients with acute abdominal pain, showing that initial US in all and CT in case of negative or inconclusive US was the optimal diagnostic imaging strategy to detect urgent disease [12]. The new Dutch acute appendicitis guidelines have been completed and became effective in March 2010. The imaging proposed in that guideline is the routine strategy in our study protocol, i.e. US in all and CT in negative or inconclusive US cases.

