This study aims to determine the optimal diagnostic strategy for patients with suspected acute appendicitis in the emergency department. If MRI is found to be sufficiently accurate, it could replace CT in some or all patients. This will limit CT related cancer induction and death and contrast medium induced nephropathy, preventing the burden and the direct and indirect costs associated with treatment. Radiation exposure of CT is especially a concern in children, pregnant patients, and adults <50 year, but not negligible in individuals ≥ 50 year. Seventy-five percent of adult patients with suspected appendicitis were < 50 year in the OPTIMA study and this proportion will be similar in this study proposal [12]. Until now MRI has almost exclusively been studied in children and pregnant patients [18]. Apart from the risk of cancer induction, CT is associated with the risk of renal insufficiency. Intravenous contrast medium aggravates existing renal insufficiency and induces renal insufficiency in those with marginal renal function [19]. Approximately 60% of patients are not aware of their (imminent) renal insufficiency. The prevalence of (imminent) renal insufficiency increases with age [20]. For MRI no intravenous contrast medium is needed, obviating this risk. MRI can be beneficial for all adult patients irrespective of age. Studying MRI in all adult patients is therefore important.

Based on the high intrinsic contrast resolution of MRI, one might envision higher accuracy rates for MRI than CT, but this needs to be substantiated in this study. If so, MRI could further decrease the number of unnecessary appendectomies and the number of missed appendicitis cases.

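### The promised comparison of MRI with CT in unselected patients cannot be made, because CT is done only when US does not confirm appendicitis

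*Protocol article*

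**What the plan says.** Two statements in the protocol article set up a comparison with CT. The Background section says: "The present study will allow us to estimate the accuracy of MRI in unselected patients and to compare with that of CT". The Discussion says of MRI that "one might envision higher accuracy rates for MRI than CT, but this needs to be substantiated in this study".

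The design gives the two tests to different groups. Under Study design, US comes first, "followed by CT in all cases in which US does not confirm the suspected appendicitis"; the Discussion describes the same routine as "US in all and CT in negative or inconclusive US cases". For MRI, Study design says: "Additionally, all patients undergo MRI, with the MRI reader blinded from the results of the other imaging methods".

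The Data Analysis section announces: "In addition, the accuracy of the following scenarios will be estimated". After clinical evaluation alone, the list runs "2) US in all patients followed by CT after a non diagnostic US, (2) US only, (3) MRI only", and ends with "4) US followed by MRI after a non diagnostic US". There is no CT-only scenario. The Sample size calculation derives 230 patients from the precision of MRI sensitivity and specificity, and mentions no comparison with CT.

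**The concern.** The promise and the design do not match. The Background promises a comparison with CT in unselected patients, but no patient whose US confirms appendicitis is scheduled for CT. The gap lies in the data to be collected, so a statistical analysis plan cannot close it.

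Replacing CT in some or all patients is the clinical use that the Discussion has in view. If the promise stands, a reader of the results may set MRI accuracy from all patients beside CT accuracy from a group already filtered by US. Those two figures would refer to different spectra and prevalences of disease, which is the weakness that the Background section finds in earlier MRI studies. The sample size also gives no assurance about how precise any MRI-CT comparison would be.

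**Working it through.** **1. The plan's own figure.** Inputs from the Sample size calculation: sensitivity 90%, specificity 95%, prevalence 60%, 95% intervals not exceeding 10%, N = 230.

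- Reading 10% as total width (half-width 0.05), n = 1.96² × 0.90 × 0.10 / 0.05² = 138.3 cases. Rounded up, 139 / 0.60 gives N = 232, in line with 230.
- The Wilson interval for 124/138 is 83.7-93.9%, matching the stated 84-94%. The Wilson interval for 87/92 is 87.9-97.7%, matching the stated 88-98%.

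So 230 reproduces, as a figure for MRI alone. (The plan prints 95 correct exclusions where 95% of 92 non-cases is 87. That is a separate slip and does not affect this point.)

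**2. Who has CT.** The protocol gives no US accuracy, so a range is assumed: US confirms appendicitis in 60-85% of cases (sensitivity) and does not confirm it in 80-95% of non-cases (specificity). An inconclusive US counts as not confirming.

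- Cases with CT = 138 × (1 − US sensitivity): 138 × 0.15 = 20.7 to 138 × 0.40 = 55.2, about 21-55 of 138.
- Non-cases with CT = 92 × US specificity: 92 × 0.80 = 73.6 to 92 × 0.95 = 87.4, about 74-87 of 92.
- All patients with CT: 20.7 + 73.6 = 94.3 to 55.2 + 87.4 = 142.6, about 94-143 of 230, or 41-62%.
- Prevalence among them: lowest 20.7 / (20.7 + 87.4) = 19%, highest 55.2 / (55.2 + 73.6) = 43%, against 60% in the cohort.

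**3. Precision in that subset.** Wilson width = 2z / (1 + z²/n) × √[p(1 − p)/n + z²/(4n²)], with z = 1.96.

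| Quantity | n | 95% width (points) |
|---|---|---|
| Sensitivity 90%, all cases | 138 | 10.1 |
| Sensitivity 90%, CT subset | 55 | 16.2 |
| Sensitivity 90%, CT subset | 21 | 26.6 |
| Specificity 95%, all non-cases | 92 | 9.4 |
| Specificity 95%, CT subset | 87 | 9.7 |
| Specificity 95%, CT subset | 74 | 10.7 |

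A wider assumption (US sensitivity 50-90%, specificity 80-100%) gives 14-69 cases with CT and widths of 33 down to 14 points for sensitivity, with 9-11 points for specificity. The conclusion is the same.

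**4. What can be compared in all 230 patients.** US then CT and US then MRI give the same result in every patient whose US confirms appendicitis. They can differ only in the rest. The difference in sensitivity between the strategies is therefore (cases with CT / 138) × the MRI-CT difference in the subset. With 21-55 cases the multiplier is 21/138 = 0.15 to 55/138 = 0.40, so a 10-point difference in the subset appears as about 1.5 to 4 points between strategies. The two comparisons answer different questions and need separate labels.

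**The case against.** The best defence is that a comparison with CT is not an objective of this study. The Study objectives section names MRI accuracy, costs, inter-observer agreement and patient acceptance. The Data Analysis section puts MRI accuracy first, and the sample size follows from it. The Discussion sentence is hedged. The Rationale for design speaks of evaluating MRI next to the current best strategy and leaves randomisation between CT and MRI to a later study. The scenario list respects the design: it omits CT alone and includes both two-test strategies, with a likelihood-ratio method for the gain from a second test. The Conclusion says that the scenario analyses will allow strategies to be compared.

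Most of this stands. It places the fault in the promises of the Background and Discussion, not in the primary aim or N. It does not remove the fault, because nowhere does the protocol limit those promises to patients whose US did not confirm appendicitis.

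A reader might go further and infer three things that the document does not support:

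- **That CT is done in only a small subset.** On the assumed range it is 41-62% of patients and nearly all non-cases. Only the appendicitis cases are few.
- **That the plan would set MRI in all patients against CT in the subset.** No section plans this.
- **That the plan estimates each strategy only separately and discards the within-patient pairing.** No section specifies an unpaired comparison, strategy comparisons are announced, and the choice of interval or test may lie in an analysis plan that is not shown.

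**Conclusion.** The point holds in limited form. As written, the promise to compare MRI with CT in unselected patients, and the implication that higher accuracy than CT can be substantiated here, go beyond what the design can deliver. The mismatch follows from the protocol text alone and needs no assumption.

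Its size does rest on assumed US accuracy. At US sensitivity 60-85% and specificity 80-95%, the direct comparison has 21-55 of 138 cases, and a 90% sensitivity would carry an interval 16-27 points wide instead of about 10. Specificity precision is nearly unchanged, at about 10-11 points. That most appendicitis cases are US-positive is also part of the assumption; the protocol says only that US gives too many false negatives.

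The estimation of MRI accuracy in all patients, and the 230 that serves it, are not affected.

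**What to change.** - **Background and Discussion** (and the Conclusion where it bears on CT): limit the comparison to two statements, namely MRI versus CT in patients whose US did not confirm appendicitis, and US then MRI versus US then CT in all patients. Drop the implication that higher accuracy than CT overall can be substantiated in this study.
- **Data Analysis:** name as the CT comparison the paired, within-patient difference in sensitivity and in specificity between US then MRI and US then CT, with a paired 95% confidence interval.
- **Data Analysis or Sample size calculation:** state the expected precision of that difference, with the assumed US accuracy and the assumed share of patients in whom MRI and CT disagree. Give the expected number of patients and cases with CT.
- **Reporting:** note that the panel sees CT but not MRI findings (Reference standard), which would tend to favour CT. The rewording does not remove this.

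The cost is a few sentences and one paired analysis of data already being collected. No extra patients or scans are needed. What is given up is the broader claim about CT, which the design could not have supported.

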## Methods/Design

### Study objectives

The OPTimizing IMaging in suspected APpendicitis (OPTIMAP) study aims to assess the diagnostic accuracy of MRI in unselected patients presenting with suspected acute appendicitis, and to estimate its costs, inter-observer agreement and patient acceptance.

### Study design

OPTIMAP is a multicenter diagnostic accuracy study of MRI in a consecutive series of adult patients with clinically suspected acute appendicitis. Consenting patients will undergo initial ultrasonography followed by CT in all cases in which US does not confirm the suspected appendicitis, which is the strategy specified in the Dutch guideline for suspected acute appendicitis. Additionally, all patients undergo MRI, with the MRI reader blinded from the results of the other imaging methods. A final diagnosis assigned by an expert panel based on all available data (except MRI) after 3 months follow-up will act as the reference standard in estimating accuracy.

### Study population

Eligible are consecutive adult patients, 18 years or older, with clinically suspected acute appendicitis presenting at the emergency department. Excluded are pregnant patients, patients with contraindications for MRI scanning and critically ill patients that need intensive vital organ function monitoring for life-support.

We will recruit patients in one university hospital (Academic Medical Center, Amsterdam) and five large teaching hospitals in the Netherlands (Medical Center Alkmaar; Antonius Hospital, Nieuwegein; Sint Lucas Andreas Hospital, Amsterdam; Gelre Hospital, Apeldoorn; Kennemer Gasthuis, Haarlem). Treating physicians in the emergency department will identify eligible patients based on medical history, physical and laboratory examination prior to imaging. Eligible patients will be informed about the study and invited to participate.

### Ethical considerations

The OPTIMAP study will be conducted according to the principles of the Helsinki Declaration and in accordance with the Medical Research Involving Human Subjects Act (WMO) and other European guidelines, regulations and acts. The Medical Ethical Committee of the Academic Medical Center in Amsterdam approved our study protocol. All participating hospitals gave their consent after assessment of local feasibility. Only patients who give written informed consent will be included in the study.

### Standard care

The findings of clinical assessment, the clinical diagnosis and possible alternative diagnoses, and the level of confidence (certainty) of the clinical diagnosis of acute appendicitis will be prospectively documented by the treating physician in an on line case record form (CRF). Subsequently a staff radiologist or radiological resident will perform an ultrasonography (US). This US concerns a complete examination of the abdomen, including the use of the graded compression technique. In case of a non diagnostic US, an abdominal computed tomography (CT) of the complete abdomen will be performed. All CT scans will be performed using a multi-detector row 4, 16 or 64 slice CT scanner (4-slice SOMATOM Volume Zoom, 16-slice SOMATOM sensation, Siemens Medical Systems, Forchheim, Germany; 16-slice MX 8000, 64-slice Brilliance, Philips Medical Systems, Best, The Netherlands; 64-slice Aquilion, Toshiba Medical Systems, Tokyo, Japan) and intravenous contrast medium. No oral or rectal contrast medium is routinely administrated. The radiologist will record imaging features of the appendix, presence or absence of appendicitis, level of confidence of the diagnosis, and possible alternative diagnoses separately in our online CRF for US or CT.

### MRI examination

Consenting patients will undergo MRI at 1.5 T (MAGNETOM Avanto 1,5 T MRI, Siemens Medical Systems, Forchheim, Germany; Intera 1.5 T MRI, Philips Medical Systems, Best, The Netherlands) within two hours of admission to the emergency department. The MRI examination will comprise breath hold axial and coronal T2 weighted sequences (HASTE: slice thickness 6 mm, FOV 400 mm, TR1500 ms, TE 90 ms, 256 × 256 matrix, flip angle 170; HASTE SPAIR: slice thickness 6 mm, FOV 400 MM, TR 1400 ms, TE 93 ms, 256 × 256 matrix, flip angle 160) and free breathing axial and coronal diffusion weighted sequences (DWI: slice thickness 6 mm, FOV 400 mm, TR 3900 ms, TE 75 ms, B-values 50 - 400 - 800, 192 × 192 matrix). A pilot study in one of the participating institutions has indicated the potential of DWI for acute appendicitis (unpublished data). No intravenous contrast medium is administrated. In-room time will be approximately 15 minutes. In two hospitals (AMC, MCA) MRI examinations will be performed between 8 AM and 11 PM, in the other hospitals during office hours.

